^ Oral vitamin C may represent a practical antioxidant due to its wide availability and lower risk of adverse effects compared with other antioxidant strategies such as intravenous vitamin C and intracameral antioxidants. Regarding these findings, we hypothesized that oral vitamin C supplementation increases ascorbic acid levels and overall antioxidant capacity in the aqueous humor and reduces oxidative stress–related endothelial damage during phacoemulsification. However, to date, no clinical studies have specifically evaluated the protective role of oral vitamin c supplementation in patients with hard cataracts undergoing phacoemulsification. On the other hand, aqueous humor will also be replaced by irrigation fluid during phacoemulsification, which may reduce the intraocular antioxidant content. Therefore, oral vitamin C is given postoperatively to restore AA levels in the aqueous humor. Thus, it is expected that the antioxidant effect of AA can suppress postoperative corneal endothelial autophagy and apoptosis, which can cause severe damage to the endothelial layer. Considering that aqueous humor sampling cannot be performed during the postoperative recovery period, it is important to determine whether the levels of MDA, TCA, and AA in the aqueous humor are the same as or correlate with blood levels, as no studies have yet examined these three biomolecular parameters simultaneously in both compartments.

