### Aims

The aim of this study is to analyze the protective effect of oral ascorbic acid supplementation on corneal endothelial cells which undergo oxidative stress due to phacoemulsification in patients with hard nucleus cataracts. The primary outcome will investigate mean change and percentage in endothelial cell density (ECD) loss prior to and after phacoemulsification, assessed at postoperative follow-up period (day 1, week 1, week 4, and week 6) of patients with hard nucleus cataracts.

The secondary endpoint will investigate mean change in other clinical parameters such as central corneal thickness (CCT), visual acuity, and cells in the anterior chamber during the postoperative follow-up period. This study will investigate differences in MDA levels in aqueous humor, prior to and after phacoemulsification, and compare between groups with vitamin C supplementation and those without. We will also investigate differences in AA, TAC, and MDA levels in serum and aqueous humor at the start of the study and after seven days of supplementation and compare them between the three groups. Furthermore, we will explore the correlation between aqueous humor and serum AA, TAC, and MDA levels.

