### Intervention

Patients will be divided into three groups, each with 40 samples. The first group (n=40) will receive 500 mg oral vitamin C three times daily (1500 mg/day) for one week before surgery to four weeks after surgery. The second group (n=40) will receive 500 mg oral vitamin C three times daily (1500 mg/day) for one week before surgery and a placebo after surgery. The last group (n=40) will receive a placebo one week before surgery to four weeks after surgery. Oral vitamin C 1500 mg/day was chosen based on pharmacokinetic evidence showing that this dosage can achieve stable plasma concentrations and approach a steady-state level during short-term administration.
^
15
^

To minimize potential bias related to surgical variability, all phacoemulsification procedures will be performed using standardized surgical techniques. The surgeries will be conducted by experienced cataract surgeons using the same phacoemulsification machine and standardized operative settings. Key intraoperative parameters, including ultrasound power, irrigation parameters, and the type of ophthalmic viscosurgical device (OVD), will be standardized across all procedures.

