Total antioxidant capacity will be measured using the QuantiChrom™ Antioxidant Assay Kit (DTAC-100, BioAssay Systems). This assay is based on the cupric ion reducing antioxidant capacity (CUPRAC) method.3.Measurement of Malondialdehyde (MDA) Levels
•MDA in Aqueous Humor:
Malondialdehyde levels in aqueous humor will be determined using a Malondialdehyde ELISA Kit (ab287797, Abcam). The principle of this assay is based on an indirect sandwich enzyme-linked immunosorbent assay (ELISA) for the quantitative detection of MDA in serum, plasma, or other biological fluids.•MDA in Blood Samples:
Malondialdehyde levels in blood samples will be measured using a spectrophotometric method based on the reaction of MDA with thiobarbituric acid (TBA) to form a pink-colored complex that can be quantified spectrophotometrically.

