### Statistical analysis

Data from this study will be recorded and analyzed by IBM SPSS 20.0. Sample personal identification, including demographic and clinical characteristics, will be reported in a descriptive analysis. Data distribution of numerical variables will be assessed using the Shapiro–Wilk test with normal distribution will be presented as mean (standard deviation [SD]); non-normal distribution will be reported as median (interquartile range [IQR]). Nominal data will be reported in frequency and percentage. We will use Pearson’s chi-squared test for categorical data. For comparisons among the three groups, one-way ANOVA will be used for normally distributed data, while the Kruskal–Wallis test will be used for non-normally distributed data. Significant group differences will be followed by post-hoc pairwise comparisons using Bonferroni correction for ANOVA or Dunn’s test following the Kruskal–Wallis analysis to account for multiple testing. Pearson’s test will be used to test the correlation between data in aqueous humor and serum. A p-value of less than 0.05 (p < 0.05) will be considered statistically significant.

Effective phacoemulsification time (EPT) and total surgical duration will be included as covariates in the statistical analysis to account for their potential influence on postoperative endothelial outcomes. Multivariable analysis will also be conducted to control for potential confounding variables, including smoking status, occupational exposure, ultraviolet (UV) light exposure, and dietary intake of vitamin C. These variables will be collected through structured questionnaires during the screening.

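### The aqueous–serum correlation is planned as one Pearson test with no adjustment for arm, so a treatment shift in both compartments can create or inflate it; for MDA the assays also differ

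*Protocol article*

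**What the plan says.** The Aims section states that "we will explore the correlation between aqueous humor and serum AA, TAC, and MDA levels". The Introduction gives the reason: aqueous humor cannot be sampled during postoperative recovery, so the investigators want to know whether marker levels "in the aqueous humor are the same as or correlate with blood levels".

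The Statistical analysis section assigns one method to this aim: Pearson's "test will be used to test the correlation between data in aqueous humor and serum". It mentions no stratification by arm, no adjustment for arm and no sampling time for this test. Group comparisons switch to Kruskal–Wallis and Dunn's test when data are not normal; no such switch is given for the correlation. The covariates named later in the section (EPT, surgical duration, smoking, occupation, UV exposure, diet) do not include arm and are not linked to the correlation.

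The Post-intervention evaluation and Laboratory analysis sections place both aqueous samples at surgery and the second blood sample after seven days of supplementation. AA and TAC are measured only in the pre-phacoemulsification aqueous sample. Under Intervention, groups 1 and 2 take vitamin C in the week before surgery and group 3 takes placebo.

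On assays, the Laboratory analysis section says "Malondialdehyde levels in aqueous humor will be determined using a Malondialdehyde ELISA Kit", while MDA in blood is read by a thiobarbituric acid (TBA) spectrophotometric method.

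**The concern.** Using blood in place of aqueous humor is a patient-level question: among patients treated alike, does a higher serum level go with a higher level in the eye? A correlation over all patients also picks up the difference between arm means. If vitamin C raises both compartments, treated patients lie high on both axes and placebo patients low on both. That alone gives a positive r, even if serum says nothing about the individual eye within an arm.

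The trial's own reasoning makes a joint shift plausible for AA and, at least on the aqueous side, for TAC. The Introduction says "we hypothesized that oral vitamin C supplementation increases ascorbic acid levels and overall antioxidant capacity in the aqueous humor", and the dose is justified on the ground that "this dosage can achieve stable plasma concentrations and approach a steady-state level during short-term administration". A significant pooled r could then be read as support for blood as a stand-in for the eye when it mainly restates the treatment effect.

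For MDA there is a second issue. With one assay per compartment, a difference in level between blood and eye cannot be separated from a difference between assays.

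**Working it through.** The plan gives no figure for this analysis, so there is none to reproduce.

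**Inputs from the protocol.** Vitamin C to placebo is 2:1 when the paired samples are taken (groups 1 and 2 against group 3), so p = 2/3. Total n is 3 × 36 = 108 at the stated minimum, or 3 × 40 = 120 as planned. The significance level is 0.05, taken as two-sided.

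**Assumed.** The treatment shifts in serum (d₁) and aqueous humor (d₂), in within-arm SDs, and the within-arm correlation ρ. The documents give none of these, so a range is shown.

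**Formula.** With v = p(1 − p) = (2/3)(1/3) = 2/9,

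pooled r = (ρ + v·d₁·d₂) / √[(1 + v·d₁²)(1 + v·d₂²)].

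For ρ = 0 and d₁ = d₂ = d this becomes (2/9)d² / [1 + (2/9)d²]:

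- d = 0.5: 0.0556/1.0556 = 0.05
- d = 1: 0.2222/1.2222 = 0.18
- d = 1.5: 0.5000/1.5000 = 0.33
- d = 2: 0.8889/1.8889 = 0.47

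The smallest r that reaches significance is 0.189 at n = 108 and 0.179 at n = 120.

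**Rejection rates** (simulation, 20,000 runs, normal data, ρ = 0):

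| Shift, serum / aqueous (SD) | Pooled r | Pooled test significant, n = 108 | n = 120 |
|---|---|---|---|
| 0.25 / 0.25 | 0.01 | 5% | 5% |
| 0.5 / 0.5 | 0.05 | 8% | 8% |
| 0.5 / 1 | 0.10 | 17% | 19% |
| 1 / 1 | 0.18 | 48% | 52% |
| 1.5 / 1.5 | 0.33 | 96% | 98% |
| 2 / 2 | 0.47 | 100% | 100% |
| 2 / 0 | 0.00 | 5% | 5% |

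After treatment is removed by centring on the vitamin C and placebo means, mean r is 0.00 and the rejection rate is about 5% in every row.

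**When a real within-arm correlation exists.** With ρ = 0.3 and equal shifts of 0.5, 1, 1.5 and 2 SD, pooled r is (0.3 + v·d²)/(1 + v·d²) = 0.34, 0.43, 0.53 and 0.63. Here treatment inflates the correlation but does not create it.

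**Different assays.** Pearson's r does not change when one variable is linearly rescaled, so different units or calibration do not by themselves bias the MDA correlation. They do prevent a comparison of levels. If the two methods respond to different things, the correlation may also be weakened.

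**The case against.** The protocol does not say that the arms are pooled, and an article may leave stratification and time point of an exploratory correlation to a fuller document. That stands as far as pooling goes: it is an inference from an unqualified test, though the natural one. What the article does fix is the method, and that method has no term for arm.

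A reader might go further and infer that the planned test will show a correlation made by treatment alone and will falsely support blood as a stand-in. The documents do not support this. They give no shift size. The artefact needs a shift in both compartments, is negligible at 0.5 SD or less, and only adds to a within-arm correlation where one exists.

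Nor do they support extending the argument fully to MDA. The Introduction's hypothesis names AA, antioxidant capacity and endothelial damage. It does not name MDA, so a joint fall of serum and aqueous MDA would be an added assumption.

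The between-arm part is not pure noise either. Whether eye and blood rise together under supplementation is of some interest, so the pooled r may be kept as description.

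The assay difference does not invalidate the planned correlation, and no test of equal levels is planned; the wish to know whether levels are the same appears only in the Introduction. Nor is the correlation the only analysis without a non-normal alternative: the multivariable analysis has none stated. The contrast is with the group comparisons only.

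**Conclusion.** The point holds in conditional form. If the arms are pooled, the planned Pearson test mixes the treatment effect with the patient-level relation that the surrogate question needs. Under zero within-arm correlation and equal shifts of 1 to 2 SD in both compartments, pooled r is 0.18 to 0.47 and is significant in 48% to 100% of trials at n = 108. At 0.5 SD the effect is slight (8%), and with a shift in one compartment only it is absent. These figures rest on assumed shifts and normal data. The point applies mainly to AA and TAC.

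For MDA, the two assays rule out a statement that levels are equal, but not a correlation. The aim is exploratory and the primary ECD analysis is untouched, so this is an inexpensive improvement rather than a flaw in the trial's main conclusion.

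**What to change.** 1. Name the pairing: day-7 serum with pre-phacoemulsification aqueous humor, for each of AA, TAC and MDA.
2. Report the arm-adjusted (within-group partial) correlation with its 95% CI, and make this the basis for any claim that blood reflects the eye. Use Spearman if the data are non-normal, judged after removing arm means, since a mixture of shifted arms can look non-normal in itself. Spearman without arm adjustment would not remove the artefact.
3. Show the pooled r beside it, if wanted, labelled as descriptive.
4. Limit MDA to correlation and make no statement that blood and aqueous levels are the same. Reading blood by the aqueous ELISA would allow a comparison of levels, but the protocol does not document spare blood for this, so the fix does not depend on it.

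**Cost.** Analysis wording only. The loss of precision is small: on Fisher's z scale at n = 108 the standard error goes from 1/√105 = 0.0976 to 1/√103 = 0.0985 when two arm terms are fitted. The reported r will probably be smaller. The article puts the study in data processing in September 2025, so the change should be recorded before the correlations are examined.

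### The primary ECD outcome gets an unadjusted three-group test and one or two covariate-adjusted analyses, all read at p < 0.05, and the plan does not say which one decides

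*Protocol article*

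**What the plan says.** The Aims section of the protocol article defines the endpoint: "The primary outcome will investigate mean change and percentage in endothelial cell density (ECD) loss prior to and after phacoemulsification", assessed at day 1 and weeks 1, 4 and 6.

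The Statistical analysis section then gives, in this order:

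- **Unadjusted comparison.** "For comparisons among the three groups, one-way ANOVA will be used for normally distributed data", with Kruskal-Wallis if the data are not normal according to Shapiro-Wilk.
- **Multiplicity.** A significant group difference leads to "post-hoc pairwise comparisons using Bonferroni correction for ANOVA or Dunn’s test following the Kruskal–Wallis analysis to account for multiple testing". This covers pairs of arms only.
- **Threshold.** "A p-value of less than 0.05 (p < 0.05) will be considered statistically significant". No analysis is exempted.
- **First adjustment.** EPT and "total surgical duration will be included as covariates in the statistical analysis to account for their potential influence on postoperative endothelial outcomes". No model is named.
- **Second adjustment.** "Multivariable analysis will also be conducted to control for potential confounding variables". The variables are smoking, occupational exposure, ultraviolet exposure and dietary vitamin C, all taken from questionnaires at screening. Again no model is named.

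No sentence calls any of these analyses primary, supportive or sensitivity.

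**The concern.** One-way ANOVA and Kruskal-Wallis have no covariate term. The two tests that the section names therefore cannot carry out the adjustment that it goes on to require, and at least one further, unnamed model of the same outcome is needed. The word introducing the multivariable analysis makes it an addition, not a replacement.

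A reader who follows the text ends up with two or three p-values for the same ECD outcome at the same visit, each comparable with 0.05. (ANOVA and Kruskal-Wallis are alternatives, so together they count once.) If the p-values disagree, nothing says which one is the trial's answer. The choice could then be made after the results are seen, and the stated 5% error rate would no longer describe the procedure used.

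**Working it through.** **1. The plan's own sample size.** The Sample size calculation section gives SD 201, difference 132, α 0.05 and power 80%. For an unadjusted, two-sided comparison of two means:

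n = 2 × 201² × (1.96 + 0.8416)² / 132² = 36.4 per arm.

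The article states 36, and 36 / 0.9 = 40 with 10% dropout. Power is 79.6% at 36 per arm and 83.6% at 40. The calculation thus rests on an unadjusted two-group comparison, but that section does not say which test decides the trial.

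**2. Upper reference.** If the tests were independent, the chance of at least one false positive would be 1 − 0.95² = 9.75% for two tests and 1 − 0.95³ = 14.26% for three. The tests share the same outcome data and are strongly correlated, so the true figure is lower and has to be simulated.

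**3. Simulation.** Three arms of 36, one visit, one ECD measure, overall F test for arm at 0.05. Three versions were run on the same data: no covariates, two covariates (standing for EPT and duration), and six covariates (adding the four questionnaire variables). Covariates are independent of arm. The article gives no figure for how much variance they explain, so R² is an assumption and is varied. The true-effect settings use SD 201 and arm means of 0/66/132 or 0/132/132. There were 4,000 to 8,000 trials per setting. Results are rounded to whole percentages, and repeat runs agreed to within about 2 points.

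| Assumed R² (two + four covariates) | No effect: any of three significant | Effect 0/66/132: unadjusted and six-covariate verdicts differ | Effect 0/132/132: same comparison |
|---|---|---|---|
| 0 | 6% | 8% | 5% |
| 0.10 + 0.05 | 8% | 13% | 10% |
| 0.30 + 0.05 | 9% | 22% | 15% |
| 0.30 + 0.10 | 9% | 22% | 15% |
| 0.40 + 0.15 | 10% | 28% | 17% |

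Each version taken alone rejects in about 5% of null trials. If only the unadjusted and the six-covariate versions count, at least one is significant in about 6% of null trials at R² = 0 and in about 7% to 9% over the other rows.

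**4. Effect of the normality step.** With Shapiro-Wilk choosing between ANOVA and Kruskal-Wallis, as the section prescribes, the any-of-three rate at R² 0.25 + 0.10 was 8.9% with 36 per arm and 9.0% with 40. With a skewed outcome and 40 per arm it was 9.8%. The selection step does not change the picture.

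**The case against.** The strongest reply is that nothing here is contradictory. The covariates are promised for the statistical analysis in general, not for the one-way ANOVA, and an unadjusted comparison followed by an adjusted one is ordinary practice. This is correct. A reader might infer that the two analyses are incompatible and cannot both stand, but the text does not support that. Both can be run, provided the adjusted model is something other than the tests named. What is missing is a ranking.

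A reader might also infer that the plan allows success on any of three tests. It does not say so. Nor is it clear that there are three: the EPT/duration sentence and the multivariable sentence may describe one model. The inflation figures are therefore conditional on a decision rule that the article neither states nor excludes, and on assumed R². The surgical standardisation described under Intervention (same machine, standardised power, irrigation and viscoelastic) could make R² small, in which case the inflation is only about one percentage point.

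Disagreement between verdicts under a true effect is not itself an error either. Adjustment is expected to change some results by adding precision.

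The order of the section and the unadjusted sample size calculation hint that the unadjusted test comes first. A hint is not a designation, and the covariate sentence concerns the endothelial outcomes specifically.

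Finally, ranking analyses and naming the model are often left to an analysis plan that is not shown here. That would answer a bare omission. Here the published text prescribes several analyses of one outcome under one threshold, and names tests that cannot perform the adjustment it requires.

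**Conclusion.** The point holds as a missing ranking and an unnamed model. The plan prescribes an unadjusted test and one or possibly two adjusted analyses for the same ECD outcome, all at p < 0.05, and does not say which decides the primary claim.

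If any significant version were taken as success, the omnibus false-positive rate would be about 6% with covariates that explain nothing, and about 8% to 10% with an assumed R² of 15% to 55%, instead of 5%. These figures are for a single visit and a single ECD measure. Under a true effect, the unadjusted and adjusted verdicts would differ in roughly 5% to 8% of trials with uninformative covariates, rising to about 28% at R² 0.55 with arm means of 0/66/132. The upper error figures also need the two adjusted analyses to be separate models.

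The inflation is moderate. The matter should be settled because verdicts could plausibly differ and because the Study status section says that data processing is already under way.

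**What to change.** In the Statistical analysis section:

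- Name one deciding test for the primary ECD outcome: a linear model (ANCOVA) with arm and a fixed list of covariates recorded before treatment. Screening already supplies candidates, namely the ECD measurement and the questionnaire variables.
- Take the pairwise arm contrasts from that model, with the Bonferroni correction already planned.
- Label the one-way ANOVA or Kruskal-Wallis, and any model containing EPT and surgical duration, as sensitivity analyses that cannot by themselves support a claim of effect. EPT and duration are recorded during surgery, after a week of supplementation, so they are not pre-treatment covariates.

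**Cost.** No new data and no extra patients, but this is more than a change of wording. EPT and duration leave the deciding model, and the sponsor gives up claiming success from an alternative version. Because the study is in data processing, the choice should be dated and made before any unblinded comparison of arms. If that is no longer possible, the report should disclose that it was made later.

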**Dissemination**

The findings from this study will be disseminated through presentations at national and international conferences and submitted for publication in peer-reviewed journals. Trial outcomes will also be reported in the trial registry (
ClinicalTrials.gov). Authorship will follow ICMJE recommendations. The investigators intend to publish the findings regardless of the direction or significance of the results.

The results of this study will provide data on the protective effect of vitamin C supplementation for corneal endothelial cells in patients with hard nucleus cataracts undergoing phacoemulsification. This will initiate further investigation for the alternative management for permanent endothelial decompensation or bullous keratopathy.

